## Abstract

**Background:**

Older people living in nursing homes are at high risk of falling because of their general frailty and multiple pathologies. Prediction of falls might lead to an efficient allocation of preventive measures. Although several tools to assess the risk of falling have been developed, their impact on clinically relevant endpoints has never been investigated. The present study will evaluate the clinical efficacy and consequences of different fall risk assessment strategies.

**Study design:**

Cluster-randomised controlled trial with nursing home clusters randomised either to the use of a standard fall risk assessment tool alongside nurses' clinical judgement or to nurses' clinical judgement alone. Standard care of all clusters will be optimised by structured education on best evidence strategies to prevent falls and fall related injuries. 54 nursing home clusters including 1,080 residents will be recruited. Residents must be ≥ 70 years, not bedridden, and living in the nursing home for more than three months. The primary endpoint is the number of participants with at least one fall at 12 months. Secondary outcome measures are the number of falls, clinical consequences including side effects of the two risk assessment strategies. Other measures are fall related injuries, hospital admissions and consultations with a physician, and costs.

## Background

Fall prevention in the elderly has been recognised as an important area of research and intervention [1]. Numerous studies have presented combinations of fall related risk factors and a number of risk assessment tools have been developed [2,3]. However, few of these tools are based on rigorous research. The minority has been adequately tested for accuracy [4]. Reproducibility and transportability have been rarely investigated [5]. An own recently conducted systematic review including 27 publications on 25 non-laboratory fall risk assessment tools found that only 13 instruments have been validated in different settings [6]. Treatment paradox has been discussed by only four publications although it seems to be an important source of bias in accuracy studies which use the number of fallers as reference standard. However, there is no other measure to use as the gold standard for determining the validity of a fall risk assessment tool. Treatment paradox is difficult to overcome as it would be unethical to discourage fall prevention measures in the clinical setting in order to test risk assessment tools. None of the publications included in the systematic review [6] reported or even discussed side effects of fall risk assessment like the application of physical restraints.

A German national nursing guideline on fall prevention discourages the use of a risk assessment tool [7]. However, as shown in a national survey these instruments are increasingly used throughout different nursing settings [8].

Only three tools have been repeatedly evaluated in geriatric populations: the Tinetti Test, the Mobility Interaction Fall Chart (MIF) and the Downton Index [9-11]. The Tinetti Test [9] and the MIF [10] are not suitable for routine nursing assessment in nursing homes as they are time-consuming and require special training whereas the Downton Index has been described to be easily administered by nurses [11]. Few accuracy studies compared fall risk assessment tools to nurses' clinical judgement [4,10,12,13]. Predictive values were unsatisfactory for both risk assessment strategies. None of the tools was superior to nurses' clinical judgement.

The impact of the use of a fall risk assessment tool on clinically relevant endpoints has never been investigated within a methodologically rigorous trial. Therefore, we designed a randomised controlled trial to compare the clinical efficacy and consequences of the use of a standard fall risk assessment tool alongside nurses' clinical judgement with nurses' clinical judgement alone. We chose the Downton Index as comparator to single nurses' clinical judgement since it has been validated in a nursing home population and its predictive value is comparable to other instruments. The Downton Index is easy to administer and is comparable to those non-validated tools already in use in German nursing homes.

## Methods

### Study design and setting

The study is a cluster-randomised controlled trial over 12 months with nursing homes randomised either to optimised standard care and the use of the Downton Index or optimised standard care alone. A full economic evaluation is also being conducted.

### Ethical considerations

The protocol has been approved by the ethics committee of the Hamburg chamber of physicians and the regional data protection office.

### Study interventions

A structured single education session of 60 to 90 minutes will be provided for all clusters to optimise standard care and to minimise possible centre effects. The education programme will cover information on best evidence strategies to prevent falls and fall related injuries. The programme is based on principles of social learning theory [14]. The development of the curriculum followed approaches we have successfully tested for other education programmes [15,16].

After randomisation nurses of the intervention group (IG) will be introduced to the use of the Downton Index. A nominated nurse in charge of each cluster will then be responsible for the monthly application of the tool. No further intervention will be carried out in the control group.

### Identification of clusters and participants

Nursing homes in the cities Hamburg and possibly Bremen, Germany, and respective catchment areas will be invited to participate. A cluster is defined as a nursing home by itself or an independently working ward of a large nursing home. In a first step, a serially numbered list of all residents of each cluster will be produced by the nurse in charge. In a second step 20 residents fulfilling the predefined inclusion criteria (≥ 70 years old, not bedridden, and living in the nursing home for more than three months) will be selected using investigators' random table. Descriptive data on the cluster and participating residents will be collected by the nurse in charge supported by the external investigators. The figure shows the summary of the trial design.

### Randomisation

We will use computer generated randomisation lists for concealed allocation of clusters. To obviate disparate sample sizes permuted blocks will be used. Clusters will be allocated by an external researcher immediately after collection of baseline data and administration of the education programme.

### Clinical outcomes measures

The primary outcome is the number of participants with at least one fall at 12 months. Secondary outcome measures are the number of falls, clinical consequences, i.e. fall and injury prevention measures applied, and side effects of the two risk assessment strategies. Side effects are defined as the application of physical or pharmacological restraints. Injuries and fractures related to falls, hospital admissions and consultations with a physician related to falls irrespective of the reason for falls, and costs will also be recorded.

Nursing staff will have to fill in a specially developed documentation sheet in case of a fall event, also a documentation sheet on measures used to prevent falls once a month.

Data will be checked monthly during personal visits of the investigators. It is not possible to objectify the documented falls. Nevertheless, in Germany, nurses are legally required to document falls in nursing homes. Interrater reliability of the Downton Index will be determined in a subgroup of nurses of the IG clusters.

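### The restraint outcome does not separate restraint already in place before allocation from restraint started afterwards, and its planned comparison uses no baseline value

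*Protocol article*

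**What the plan says.** **Definition.** Under Clinical outcomes measures, a secondary outcome is "side effects of the two risk assessment strategies", with the definition "Side effects are defined as the application of physical or pharmacological restraints". The wording contains no reference to new use, to use after allocation, or to change from a starting value.

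**Recording.** The same section has nursing staff fill in a sheet for each fall and "also a documentation sheet on measures used to prevent falls once a month". This is the only described form on which restraint could be recorded.

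**Entry.** Identification of clusters and participants lists three criteria: "≥ 70 years old, not bedridden, and living in the nursing home for more than three months". None concerns restraint, so a resident who is restrained but not bedridden can be enrolled.

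**Baseline.** The same section says "Descriptive data on the cluster and participating residents will be collected by the nurse in charge", without naming any variable. Under Randomisation, clusters are allocated "immediately after collection of baseline data and administration of the education programme", so baseline collection comes first.

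**Analysis.** For every outcome other than the primary one, Statistical analysis makes the cluster the unit of analysis and compares the groups by a Wilcoxon rank sum test on follow-up data. No baseline term is stated.

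**The concern.** A restraint in use before the Downton Index was introduced cannot have been caused by it. If it continues after allocation, the printed definition still allows it to be counted as a side effect of whichever strategy the cluster receives. Two analysts working from the same monthly sheets could report different side-effect rates, depending on how they read the definition.

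The comparison between arms is affected too. Pre-existing restraint adds events to both arms and variation between clusters, and the planned test has no means of removing either.

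The Background makes this question prominent: it says that none of the reviewed publications "reported or even discussed side effects of fall risk assessment like the application of physical restraints". Restraint is the only side effect that the article names. The error to fear is false reassurance, in which a real increase is missed because it is small against a large and variable background.

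**Working it through.** **1. The plan's own figure.** The article sizes only the primary outcome. Inputs from Sample size calculation: 45% versus 30% fallers, ICC 0.075, about 20 per cluster, 20% loss, two-sided alpha 0.05, power 80%.
- Design effect: 1 + 19 × 0.075 = 2.425, as stated.
- Two proportions with continuity correction: 176 per arm.
- Total: 2 × 176 × 2.425 / 0.80 = 1,067. Divided by 20, this is 53.35 clusters, rounded up to 54, or 1,080 participants.

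The stated 1,080 is reproduced. It does not depend on how restraint is defined. The article gives no rate, ICC or expected effect for restraint, so everything below rests on assumptions.

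**2. Dilution.** Assume new restraint in 10% (control) and 20% (Downton Index) of residents unrestrained at entry, and that all existing restraint continues. With baseline prevalence π, the follow-up proportions are π + (1 − π) × 0.10 and π + (1 − π) × 0.20. Completers: 1,080 × 0.80 = 864, or 432 per arm. The effective number per arm is 432 / 2.425 = 178. Power is by normal approximation.

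| π | Control | Downton | Difference | Ratio | Power, all restraint | Power, new only |
|---|---|---|---|---|---|---|
| 0% | 10% | 20% | 10 points | 2.00 | 76% | 76% |
| 10% | 19% | 28% | 9 points | 1.47 | 52% | 71% |
| 20% | 28% | 36% | 8 points | 1.29 | 37% | 66% |
| 40% | 46% | 52% | 6 points | 1.13 | 20% | 54% |

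**3. Chance imbalance.** With 27 × 20 = 540 residents per arm, the standard error of the between-arm difference in baseline prevalence is √(2π(1 − π) × 2.425 / 540). At π = 20% this is 0.0379, so the 95% range is about ±7.4 points, against a diluted effect of 8 points. This is noise and not bias: with no true effect, the simulated cluster-level Wilcoxon test on all restraint rejected in about 4-6% of runs.

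**4. Which analysis recovers the loss.** Simulation with 27 clusters per arm, 16 followed residents each (20 less 20%), baseline prevalence 25% and baseline ICC 0.075 to 0.15 (the new-only figure in the second row is for ICC 0.075):

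| Assumed effect of the tool | Total restraint, unadjusted | Total restraint, baseline-adjusted | New restraint only |
|---|---|---|---|
| Initiation only: 8% vs 16% new, existing restraint all continues | 21-26% | 68-70% | 68-69% |
| Continuation only: 60% vs 90% continued, 8% new in both arms | 33-47% | 82-87% | about 5% |

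Baseline adjustment beat the unadjusted test in every effect scenario simulated. Counting only new restraint does as well as adjustment when the tool changes initiation, but has no power when the tool changes continuation.

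**The case against.** **The article is a condensed account.** It itemises no baseline variables at all, so the absence of restraint from them proves nothing. A full protocol or analysis plan may already record it. This stands, and the point is therefore confined to what is printed: a definition and a named test. Neither refers to the state before allocation.

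**The wording can be read as newly applied.** A side effect of a strategy is naturally something that the strategy brings about. This also stands: the text does not establish that continued restraint will be counted. It does not exclude it either, and a monthly record of measures used would capture continued use.

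**Bias between arms.** A reader might infer that pre-existing restraint can systematically imitate harm or benefit. The documents do not support that. Clusters are randomised, imbalance is by chance, and the test's type I error already covers it.

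**Eligibility.** A reader might also infer that restrained residents should not have been admitted. That is no flaw: excluding them would narrow the population.

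**Counting new restraint only.** This looks like the obvious redefinition, but it is a trade-off. Total restraint use is a legitimate outcome, because a tool that keeps residents restrained also does harm. All clusters receive fall-prevention education, so withdrawal of restraint is plausible, and a new-only count would miss it. In a further assumed case at ICC 0.075, where the tool changes both initiation and continuation, the unadjusted total had 85-95% power against 64-75% for new-only.

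**Conclusion.** The point holds in a limited form. As printed, the definition does not separate prior from new restraint, and the planned comparison ignores the baseline level. The consequences are possible mislabelling of continued restraint as a side effect within each arm, and a loss of power for a true increase. There is no systematic bias between the arms.

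The direction of the power loss was the same in every effect scenario simulated; its size is not known. The figures of 21-26% versus 68-70%, and 33-47% versus 82-87%, depend on assumed restraint rates, clustering and effects. They should not be read as the trial's actual power. The outcome is secondary and the trial was not sized for it, so this is a worthwhile, inexpensive improvement. It does not threaten the primary analysis.

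**What to change.** 1. Leave the entry criteria unchanged.
2. Complete the existing measures sheet once per participant with the baseline data, before allocation, recording physical and pharmacological restraint. If the full protocol already does this, say so in the definition. It has to be done before allocation, because baseline status cannot be reliably reconstructed later.
3. Keep total restraint use as the outcome and state that it includes continued use. Compare the arms at cluster level, adjusted for the cluster's baseline restraint prevalence or as change from it. A Wilcoxon test on the cluster changes would stay close to the present plan.
4. Report newly started restraint among residents unrestrained at baseline as a supporting analysis and not as a replacement.

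The cost is one extra completion of an existing sheet per participant, at a stage when baseline data are collected anyway, and slightly more analysis. No additional visit, form or participant is needed.

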### Sample size calculation

It is assumed that about 45% of the participants in the control group will experience at least one fall in 12 months with an intra-class correlation coefficient of ICCC = 0.075. A cluster-randomisation with about 20 participants in each cluster leads to a variation inflation factor of VIF = 2.425. Assuming that 20% of the participants will not complete follow-up and furthermore assuming an absolute difference of 15% (incidence of fallers in the Downton Index-group: 30%) to reach a significant result to the level of alpha = 0.05 with a power of 80% a total sample size of n = 1,080 participants is needed. Therefore the sample size comprises a total of 54 clusters with about 20 participants each.

### Statistical analysis

The main outcome is the proportion of persons with at least one fall and will be analysed by using a chi-square test adjusted for cluster randomisation [17]. The effect of the risk assessment tool will be expressed as relative risk, difference in absolute risk, and number needed to treat. For risk differences 95% confidence intervals will be calculated using a method appropriate for cluster-randomised trials [18]. For all other follow up data the cluster will be used as unit of analysis. For statistical comparisons between the groups the Wilcoxon rank sum test will be performed. Two-sided p ≤ 0.05 will be regarded as significant. Interrater reliability will be calculated using kappa statistics.

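### The primary cluster-adjusted chi-square is valid, but it cannot use baseline data collected before allocation; a prespecified covariate-adjusted cluster analysis could gain precision at little cost

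*Protocol article*

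**What the plan says.** The Statistical analysis section of the Protocol article names one primary test: the proportion with at least one fall "will be analysed by using a chi-square test adjusted for cluster randomisation". It adds that "For risk differences 95% confidence intervals will be calculated using a method appropriate for cluster-randomised trials" and that "Two-sided p ≤ 0.05 will be regarded as significant". The effect is to be reported as relative risk, risk difference and NNT. No baseline covariate enters the primary comparison.

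Under Identification of clusters and participants, "Descriptive data on the cluster and participating residents will be collected by the nurse in charge", with help from the investigators. A cluster may be a whole home or one ward of a large home. The Randomisation section places allocation directly after baseline collection and the education session. Its stated purpose for blocking is numerical: "To obviate disparate sample sizes permuted blocks will be used".

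The Sample size calculation section assumes that about 45% of control residents "will experience at least one fall in 12 months with an intra-class correlation coefficient of ICCC = 0.075". It also says: "A cluster-randomisation with about 20 participants in each cluster leads to a variation inflation factor of VIF = 2.425".

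**The concern.** Variables measured before allocation are legitimate covariates, and this trial collects them at both cluster and resident level. An ICC of 0.075 means that clusters are expected to differ materially in fall risk, and only 54 of them are allocated. If higher-risk clusters fall by chance into one arm, a comparison of two proportions cannot correct for it. An adjusted analysis chosen after the imbalance has been seen would be open to dispute.

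This concerns a choice that the article makes. It names the primary test, so a later analysis plan that made an adjusted model primary would change the stated analysis; it would not be filling in a detail. At stake are the precision of the primary estimate and its protection against an unlucky allocation.

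**Working it through.** **Inputs.** From the Sample size calculation section: 45% versus 30%, ICC 0.075, 20 residents per cluster, 20% loss, 54 clusters, 80% power, alpha 0.05 (two-sided under Statistical analysis). Assumed here: 27 clusters per arm (1:1), and 0.8 × 20 = 16 residents analysed per cluster.

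**1. The plan's own figure.** VIF = 1 + 19 × 0.075 = 2.425, as stated. The two-sided, continuity-corrected formula for 45% versus 30% gives 176 per arm. Then 176 × 2.425 = 426.8, and 426.8 / 0.8 gives 534 per arm, or 1,068 in total. At 20 per cluster this rounds up to 54 clusters and 1,080 residents, so the stated size reproduces. (Without the continuity correction it is 163 per arm and 990 in total, which does not match.)

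**2. Chance difference in underlying risk between arms.**
- Between-cluster SD = √(0.075 × 0.45 × 0.55) = 0.136, or 13.6 points.
- SD of the arm difference = 0.136 × √(2/27) = 0.037, or 3.7 points.
- 95% limit = 1.96 × 3.7 = 7.3 points.
- The chance of an imbalance of 7.5 points or more is about 4%.
- At 45%, the 95% limit runs from 4.2 to 8.4 points for an ICC of 0.025 to 0.10.

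**3. Share of the total variance.** The variance of a cluster proportion is proportional to 0.075 + 0.925/16 = 0.1328. At 45% in both arms, the SE of the difference is √(2 × 0.2475 × 0.1328 / 27) = 0.049, or 4.9 points. The between-cluster share of the variance is 0.075 / 0.1328 = 56%. The 3.7 points are thus a component of the planned standard error, not an addition to it.

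**4. Validity of the planned test.** Unstratified allocation of 54 clusters was simulated (20,000 trials per scenario, 16 analysed per cluster), with half of the between-cluster variance due to a binary cluster factor. The cluster-adjusted chi-square rejected in 5.6–5.7% of null trials; an ordinary chi-square rejected in about 18%. Power at a 15-point difference was about 86%.

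**5. Power without covariates at 15 points.** With 432 completers per arm (540 × 0.8) and VIF 2.425, the effective size is 178 per arm and power is 83.5%. With VIF 1 + 15 × 0.075 = 2.125 for 16 completers, the effective size is 203 and power is about 88%.

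**6. Possible gain.** The shares explained are assumptions; the article gives no basis for them.
- None explained: ratio 1, no gain.
- 25% between and 5% within: (0.75 × 0.075 + 0.95 × 0.0578) / 0.1328 = 0.837, so 16% less variance.
- 50% between and 10% within: (0.50 × 0.075 + 0.90 × 0.0578) / 0.1328 = 0.674, so 33% less variance.

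Power is Φ(difference/SE − 1.96), with SE = √{[p₁(1−p₁) + p₂(1−p₂)] × 0.1328 / 27 × ratio}:

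| True difference | Ratio 1 | Ratio 0.837 | Ratio 0.674 |
|---|---|---|---|
| 15 points (45% v 30%) | SE 0.0474, 88% | SE 0.0434, 93% | SE 0.0390, 97% |
| 10 points (45% v 35%) | SE 0.0483, 54% | SE 0.0442, 62% | SE 0.0397, 71% |

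The 10-point row is an illustration and is not the trial's target.

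**The case against.** The strongest reply is that nothing is broken. The test and the interval allow for clustering, the ICC is built into the sample size, and power at the planned difference already exceeds 80%. To say that chance imbalance may create or mask an effect is largely to restate alpha and beta. All of this stands, and it limits the point to efficiency and robustness.

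The size of the gain is also uncertain. Every figure above zero in step 6 rests on assumed shares. The Background section reports that predictive values were unsatisfactory both for fall risk tools and for nurses' judgement, which does not encourage optimism. Nor is a usable fall history assured. Residents have been in the home for over three months and nurses must by law document falls, but the article does not say that earlier falls are on the baseline form. It also concedes that recorded falls cannot be objectively verified. These limits stand too.

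A reader might go further and infer that randomisation is unstratified, or that the baseline data go unused. The article does not support either. It names no strata and no adjusted analyses, but a condensed article commonly leaves these to fuller documents, and the data serve at least for description. The point therefore makes no demand on the allocation scheme, the more so because the Time plan shows that cluster recruitment had already begun.

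What the reply does not remove is that the named primary test takes no covariates, and that the time to prespecify adjustment is before outcomes are known.

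**Conclusion.** The point holds as an improvement to a valid analysis. The planned test forgoes whatever precision the pre-allocation data could offer and cannot correct a chance imbalance in them. Between-cluster variation contributes an SD of about 3.7 points to the arm difference, a quarter of the 15-point target.

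A reader might take the 7.3-point limit to mean that imbalance of half the target effect (7.3/15 = 48%) is to be expected, or that the result would be biased. Neither follows. That figure is the 95% limit, and the standard error already contains it.

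The benefit of adjustment lies between nothing and about 16–33% less variance under the assumed shares. It repairs no shortfall at the planned difference and would matter more if the true effect were smaller. The figures rest on the article's 45% and ICC of 0.075, on 27 clusters per arm and on 16 residents analysed per cluster.

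**What to change.** Amend the primary analysis, before 12-month outcomes are known, to a prespecified covariate-adjusted cluster analysis. Suitable forms are GEE with small-sample-corrected standard errors, or a two-stage cluster-level analysis. Use a short fixed list of baseline variables already collected, such as age, sex and cluster type (whole home or ward). Add documented prior falls if they are on the baseline form or can readily be extracted. Standardise the model's predictions so that the relative risk, risk difference and NNT are still reported, with clustered intervals. Keep the cluster-adjusted chi-square as a supportive analysis.

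The cost is a change of analysis wording, slightly more modelling and possibly a small extraction from nursing records. It needs no extra residents or clusters and no change to the allocation.

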### Economic evaluation

The economic evaluation will adopt the viewpoint of the German health and nursing care insurance, adding up all costs and savings relevant from the viewpoint of health care insurers and party payers. Assessment will include costs for optimisation of usual care for both groups, costs for using the fall risk assessment tool in the IG as well as medical and nursing care costs following falls for both groups. Costs for the interventions will be estimated based on information from trial records. The analysis will adopt an incremental approach such that data collection will concentrate on resource use differences between study groups. The process of collecting data on resource use will be undertaken separately from data collection on unit costs. Resource use data due to fall related health care will be collected by the investigators during the personal visits using a cost component protocol. The documentation sheet has been successfully evaluated in a recent economic evaluation of a randomised controlled trial [19]. Unit costs will be collected from different sources including published data, health insurances, and various health care providers.

At present, it is not possible to state with certainty which form of economic analysis will be employed, since this will be driven in part by the clinical study results. If a difference in the primary endpoint is observed, then a cost efficacy analysis will be conducted. Otherwise a cost comparison analysis will be conducted. Since cost data will be available for the duration of the trial only, the appropriate effectiveness measure is the one that allows treatment effects during the trial only. A sensitivity analysis on the key variables that might influence the result of the economic evaluation will be carried out.

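### Read plainly, the plan compares costs with a rank test on cluster values, but the economic question is about mean or total cost

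*Protocol article*

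**What the plan says.** The Statistical analysis section of the protocol article gives the main outcome a cluster-adjusted chi-square test with its own effect measures. It then turns to the rest: "For all other follow up data the cluster will be used as unit of analysis". The next sentence is "For statistical comparisons between the groups the Wilcoxon rank sum test will be performed", followed by "Two-sided p ≤ 0.05 will be regarded as significant". No other between-group test is named for these data.

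The Clinical outcomes measures section ends its list of outcomes with "and costs will also be recorded", so costs are follow-up data.

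The Economic evaluation section describes the cost question as "adding up all costs and savings relevant from the viewpoint of health care insurers and party payers". It takes an incremental approach and counts the cost of using the tool in the intervention group, plus medical and nursing care costs after falls in both groups. If the primary endpoint shows no difference, the economic result is to be a cost comparison. The section gives no test or interval for the cost difference and does not exempt costs from the Wilcoxon rule.

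**The concern.** An insurer's total cost is the number of residents times the arithmetic mean cost per resident. The Wilcoxon rank sum test asks whether values in one group tend to exceed those in the other. The two questions agree when the groups' distributions differ by a simple shift. This design gives reason to expect something else. The tool is applied monthly in every intervention cluster, so its cost is small and present throughout that group. Any saving would come from fewer falls that lead to expensive care, which are few and large. A rank test gives full weight to a small constant shift and almost none to how large an avoided cost was.

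At stake is the direction of the economic conclusion. It matters most if the primary endpoint shows no difference, because the cost comparison is then the economic result.

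**Working it through.** **Inputs from the article.** 54 clusters of about 20 residents, ICC 0.075, about 45% fallers in the control group, two-sided 0.05. The stated inflation factor is reproduced: 1 + (20 − 1) × 0.075 = 2.425. Equal allocation, hence 27 clusters per arm, is assumed.

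**Inputs that are assumptions.** The article gives no costs. Assumed here are costly fall-related events averaging 6,000 euro, a fixed tool cost per intervention resident, and a minor cost per faller varied from 0 to 1,000 euro.

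**Scenarios.** Mean cost per resident, before the minor cost common to both arms, is tool cost + event risk × 6,000:

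| Control events | Intervention events + tool cost | Control mean | Intervention mean |
|---|---|---|---|
| 4% | 3% + 60 | 240 | 60 + 180 = 240 |
| 6% | 4% + 120 | 360 | 120 + 240 = 360 |
| 8% | 5% + 180 | 480 | 180 + 300 = 480 |
| 5% | 3% + 60 | 300 | 60 + 180 = 240 (true saving of 60) |

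**Mechanism by hand, first scenario, no minor costs, ignoring clustering.** The chance that a cluster of 20 has no costly event is 0.96^20 = 0.442 in control and 0.97^20 = 0.544 in intervention. A control cluster without an event costs 0 per resident, and every intervention cluster costs at least 60, so such a control cluster always ranks lower. One average event adds 6,000 / 20 = 300 per resident, so an intervention cluster without an event usually ranks below a control cluster with one. Where both have events, take an even chance. The probability that a random intervention cluster ranks above a random control cluster is then roughly 0.442 + (1 − 0.442) × (1 − 0.544) × 0.5 = 0.442 + 0.127 = 0.569. It exceeds one half although the means are equal.

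**Simulation with ICC 0.075, 27 clusters of 20 per arm.** Share of trials with a significant Wilcoxon result naming the intervention as dearer (nominal 2.5% in that direction):

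| Scenario | Ordinary falls cost nothing | Each faller also costs about 1,000 |
|---|---|---|
| 4% v 3% + 60, equal means | 68% | about 5–7% |
| 6% v 4% + 120, equal means | 35% | about 5–7% |
| 8% v 5% + 180, equal means | 18% | about 5–7% |
| 5% v 3% + 60, true saving of 60 | 36% | about 3% |

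A Welch t-test on cluster means rejected in about 4–6% in total at equal means.

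**Second set of assumptions.** Here there were 16 completers per cluster (20 less 20% loss), events with between-cluster correlation 0.02, and routine costs varying between clusters in place of the cost per faller:

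- Equal means (tool cost 100, events 3.3% v 5%; 100 + 200 = 300 = 5% × 6,000): intervention called dearer in 37% with no routine cost, then 35%, 27%, 11% and 6% at a routine-cost SD of 20, 50, 100 and 200.
- True saving of 50 (tool cost 100, events 2.5% v 5%; 100 + 150 = 250 v 300): 26%, then 27%, 18%, 6% and 3%.
- Rarer events (tool cost 60, events 1% v 2%; 60 + 60 = 120 = 2% × 6,000): 95%, then 94%, 50%, 15% and 5%.
- Identical cost distributions in both arms: Wilcoxon rejected in about 4–5.5% in total. The test itself is sound; it answers a different question.

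Both sets show the same pattern. The error runs towards calling the intervention dearer, is large when rare events dominate cluster costs, and fades as ordinary cost variation grows.

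**The case against.** The strongest objection is that the article never says in so many words that costs will be tested with Wilcoxon. The economic evaluation has its own section, with its own viewpoint, cost categories and sensitivity analysis, and it deliberately leaves the form of analysis open. One may read the Wilcoxon rule as covering clinical outcomes only, with cost inference left to a fuller plan that is not shown. This stands in part. It rules out treating the rank test as a settled choice for costs and lowers the severity. It does not remove the point: the rule covers all other follow-up data, costs are listed among those data, and no other method is named.

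The second objection concerns size. Rates such as 68% need a world in which residents without a major event have no fall costs at all. The article points elsewhere: about 45% of controls are expected to fall, and fall-related physician consultations and care costs are counted. This stands as well. The high rates are one end of a range whose other end is close to nominal.

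A reader might also infer from the same sentence that restraints ("Side effects are defined as the application of physical or pharmacological restraints") and the number of falls get only a p-value. The article does not support that. A Wilcoxon test on cluster values is a valid way to respect clustering for those outcomes. The statement "For risk differences 95% confidence intervals will be calculated using a method appropriate for cluster-randomised trials [18" is not limited to one outcome. Effect estimates for secondary outcomes are also commonly left to a full protocol or analysis plan.

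**Conclusion.** The point holds for costs only and is of moderate severity. On its plain reading, the article's one rule for non-primary outcomes tests ranks of cluster values, while its economic question is a difference in mean or total cost. Because the tool's cost is certain and one-sided and the savings would be infrequent and large, that test can name a cost-neutral or slightly cheaper intervention as dearer.

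The size cannot be fixed from the article. At equal true means it runs from about 18–68% when ordinary falls cost nothing to about 5–7% when each faller costs about 1,000 euro, against a nominal 2.5%. With a true saving of 60 euro it runs from 36% to about 3%. These ranges rest on the assumed event costs, event rates and tool costs, on equal allocation and on an ICC stated for fallers. A reader might infer that the trial's cost result will probably be wrong; the documents do not support that, because realistic variation in ordinary fall costs may remove most of the distortion. Nothing here touches the primary endpoint, its analysis or the sample size of 1,080.

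**What to change.** State in the Statistical analysis section that the Wilcoxon rule does not govern costs. In the Economic evaluation section, name the estimate: the arithmetic mean cost difference per resident, with a 95% confidence interval from a bootstrap that resamples whole clusters, or from a Welch t-test on cluster means. Keep Wilcoxon on costs as a supportive analysis at most. If a separate economic analysis plan already does this, a cross-reference is enough.

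The change costs wording only: no extra data and no change to the sample size. There are two downsides. The mean-based interval relies on approximate normality with about 27 clusters per arm and skewed costs. It will also be wide: with a true saving of 50 per resident under the second set of assumptions, Welch rejected in only about 4–6% of trials. That imprecision is a property of the data, and the interval would show it.
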